It is possible that the presence of HIV-1 drug resistance is not independently associated with the risk of HIV-1 transmission, and the likelihood of transmission is proportional to the quantity of virus in the genital tract [120-123]. Given that HIV-1 RNA levels in seminal plasma are highest in the first few months following HIV-1 acquisition [124, 125] and sexual transmission from source partners with primary HIV-1 infection contributes to some significant proportion of overall HIV-1 incidence [126-130], it is possible that individuals with primary HIV-1 infection may contribute disproportionately to the transmission of HIV-1 drug resistance. Transmission of drug resistance from ARV-naïve sources has been previously documented following mother-to-child [131], heterosexual [132], and same-sex [25, 113] transmission; clusters of newly-infected subjects with transmitted HIV-1 drug resistance mutations have also been identified [133-135]. In contrast, even if individuals with established infection who are receiving ARV therapy have HIV-1 drug resistance in genital fluids, they are also likely to have lower levels of HIV-1 in the male [124] and female [136] genital tracts and, consequently, a lower risk of HIV-1 transmission [121].

The low transmission fitness of HIV-1 drug resistance has been suggested by population-level analyses that have found that HIV-1 drug resistance mutations occur in smaller proportions of newly-infected individuals compared to hypothetical cohorts of potential transmitters [35-38]. All but one of these models fails to account for transmission that occurs from source partners who also have primary HIV-1 infection. In this one model, when the authors increased the estimated proportion of transmission that occur from persons with primary HIV-1 infection from 30% to 50%, HIV-1 drug resistant viruses were no less likely to be transmitted than wild-type viruses [38]. In contrast, empiric studies of transmission pairs have reported high concordance of HIV-1 drug resistance mutations in source and recipient partners when tested by consensus sequencing [19, 21, 25, 39, 40]. These studies indicate that it may not be possible to infer individual-level estimates of the risk of transmission HIV-1 drug resistance from simple population-based models, and additional research with confirmed partner-pairs is needed to identify the factors associated with transmission of HIV-1 drug resistance between individuals.

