**Aim #3: Compare HIV-1 drug resistance patterns in PIC subjects and their source partners.**

Primary objective:

1) Quantify the probability of transmission of HIV-1 drug resistance mutations from source partners.

Secondary objectives:

1) Explore whether the probability of transmission differs for specific drug resistance mutations.

2) Explore whether HIV-1 drug resistance mutations are found at different levels in recipient partners compared to confirmed source partners.

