Analysis for the primary objective will be calculated as a binomial probability of the number of mutations transmitted from each source partner to the recipient partner, conditional on the number of mutations in the source partner. This accounts for the fact that source partners will undoubtedly have different numbers of HIV-1 drug resistance mutations. For the purpose of sample size calculations, we assume that the number of mutations in the source partners follows a Poisson distribution with the expected number of mutations being two. Power calculations are based on simulations, repeated 1000 times. Each simulation estimates the binomial probability of transmitting a mutation conditional on the number of mutations in the source partners, and calculates the associated 95% confidence intervals based on normal approximation for the estimated probability. The type II error is calculated as the number of simulation replicates where the 95% confidence interval contains the value of 1, when the simulated transmission probability is less than 1.

Using the simulation analyses described above, we will have 82% power to detect a transmission probability of all source partner mutations of 80% or less if we have 17 confirmed partner-pairs in which the source partner has at least one HIV-1 drug resistance mutation. *Overall, the subset of recipient partners who had resistance identified by OLA (4/12=33%) was similar to the population studied in the pilot project. Of the 18 confirmed partner pairs without complete OLA testing, we would expect 6 to 18 source partners to have HIV-1 drug resistance. Based on our prior experience with confirming putative source partners, we would expect that the relationship of 14 of the remaining 17 partner-pairs would be confirmed, and 5 to 17 of these source partners would have HIV-1 drug resistance. We would therefore need to enroll at most 21 (and likely fewer) new putative source partners in order to have at least 6 additional confirmed source partners with HIV-1 drug resistance.*

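### Aim 3's stated power rests on a normal-approximation interval judged against the boundary value 1; carried into the analysis, that interval would understate the uncertainty of a transmission probability near 1

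*Protocol*

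**What the plan says.** The primary objective of Aim 3 (Protocol 5.b) is to "Quantify the probability of transmission of HIV-1 drug resistance mutations from source partners". Protocol 5.c.3 describes the primary analysis as a binomial probability conditional on the number of mutations in each source partner. That sentence names no interval.

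The interval appears only in the sample-size text that follows. There "we assume that the number of mutations in the source partners follows a Poisson distribution with the expected number of mutations being two". The text continues: "Power calculations are based on simulations, repeated 1000 times". Each replicate estimates the transmission probability and "calculates the associated 95% confidence intervals based on normal approximation for the estimated probability". The type II error is "the number of simulation replicates where the 95% confidence interval contains the value of 1". The result is "82% power to detect a transmission probability of all source partner mutations of 80% or less", given "17 confirmed partner-pairs in which the source partner has at least one HIV-1 drug resistance mutation". Section 1 repeats this figure to answer the criticism that the partner study may be underpowered.

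On plausible values, section 3.e says that "empiric studies of transmission pairs have reported high concordance of HIV-1 drug resistance mutations", a statement it limits to testing by consensus sequencing. Section 5.c.3 hypothesises that most, but not every, source mutation will be found in the recipient.

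**The concern.** A normal-approximation (Wald) interval for a proportion is least reliable near 0 or 1, and here the decision rule looks exactly at 1. If all mutations are transmitted, the estimated standard error is zero and the interval is the single point 1. If only a few are not transmitted, the upper limit goes above 1, so the rule says 1 cannot be excluded although a non-transmission has been seen.

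Two things are at stake. The first is the estimate: section 5.h.4 intends the Aim 3 probabilities for mathematical models, and an interval that is too narrow, or has no width, would pass false precision to them. The second is the sample-size argument: the 82%, and with it the target of 17 pairs, depends on how this interval behaves at the boundary.

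**Working it through.** **Inputs (Protocol 5.c.3).** 17 pairs; Poisson mean 2 mutations per source; true probability p = 0.80; 95% level (z = 1.96); failure if the interval contains 1; 1000 replicates.

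**1. Number of mutations.** Plain Poisson: 17 × 2 = 34. If each source must have at least one mutation, the zero-truncated mean is 2/(1 − e⁻²) = 2.31, and 17 × 2.313 = 39.3.

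**2. Reproducing the 82%.** Power is P(upper limit < 1) at p = 0.80.

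| Version | Plain Poisson | Zero-truncated |
|---|---|---|
| Pooled over all mutations, p̂ ± 1.96√(p̂(1−p̂)/n), averaged over the random n | 90.7% | 95.9% |
| Pooled, fixed n = 34 or 39 | 93.0% | 96.7% |
| Mean of per-pair proportions, between-pair SD, 200,000 replicates | 82.2% | 90.1% |

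The Monte Carlo standard error of the plan's figure is √(0.82 × 0.18/1000) = 1.2 points. Only the pair-level interval with plain Poisson counts, dropping sources that draw zero mutations, gives 82%.

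**3. Behaviour at the boundary (pooled).**

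| Not transmitted | n = 34 | n = 39 |
|---|---|---|
| 0 | [1, 1] | [1, 1] |
| 1 | [0.914, 1.027] | [0.925, 1.024] |
| 3 | [0.816, 1.007] | [0.839, 1.007] |
| 4 | [0.774, 0.991] | [0.802, 0.993] |

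So at least four non-transmissions are needed to exclude 1.

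**4. Coverage.** The sum of binomial probabilities over outcomes whose interval contains p, with independent mutations:

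| p | Pooled, n = 34 | Pooled, n = 39 | Pooled, averaged over n (plain / truncated) | Pair-level (plain to truncated) |
|---|---|---|---|---|
| 0.80 | 91.9% | 89.8% | 92.3% / 92.6% | about 90% |
| 0.90 | 86.2% | 90.8% | 88.7% / 89.8% | 84–85% |
| 0.95 | 82.4% | 86.2% | 81.4% / 85.9% | 75–78% |

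At p = 0.95 the collapsed interval [1, 1] explains nearly all of the pooled shortfall. Its probability is 0.95³⁴ = 17.5% or 0.95³⁹ = 13.5%. For comparison, averaged over the random n at 0.90–0.95, Wilson covers 95–96% and Clopper-Pearson 97–99%.

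**5. What should be reported when all are transmitted.** The Clopper-Pearson lower limit is 0.025^(1/n): 0.897 for n = 34 and 0.910 for n = 39. If mutations within a source travelled entirely together, the effective n would be 17 and the limit 0.025^(1/17) = 0.805. The Wald interval gives 1 in every case.

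**6. Power against 1 under an exact or score interval.** Either interval has an upper limit below 1 after any single non-transmission. Power at p = 0.80 is therefore 1 − 0.8ⁿ, which exceeds 99.9% for n = 34 and for n = 39.

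**The case against.** The strongest objection concerns attribution. A reader might infer that the protocol fixes the normal approximation as Aim 3's reported interval. The text does not support that: the words sit inside the power simulation, and the reporting interval may properly be set in an analysis plan that is not shown. This stands, so everything about the reported estimate is conditional on the interval being carried over.

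Other objections also stand in part:

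- **The pooled model did not produce the 82%.** It gives about 91–97%. This weakens any claim that the pooled coverage describes the sponsor's own calculation. It does not rescue the interval, because the pair-level version that does reproduce 82% covers less at 0.90 and 0.95.
- **Values near 1 are not established.** One might read section 3.e as pointing there, but that concordance was seen with consensus sequencing, while Aim 3 uses the oligonucleotide ligation assay to include low-frequency variants. Section 3.e also cites population analyses suggesting low transmission fitness, and the design value is 0.80 or less. At 0.80 the shortfall is modest. Values of 0.90–0.95 are an assumption about where the result might fall.
- **Type I error.** Non-coverage of 9–18% could be mistaken for inflated false rejection. It is not: if the true probability is 1, every mutation is transmitted, the interval is [1, 1] and 1 is never rejected. The rule is conservative.
- **A better interval does not repair the test.** Under Wilson or Clopper-Pearson, one non-transmission, or one mutation the assay misses, excludes 1. This is correct, and it is why the power statement has to change along with the interval.

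**Conclusion.** The point holds in a conditional form. The one interval the protocol names for Aim 3 is poorly suited to a comparison with 1. If it is used for the reported estimate, nominal 95% coverage becomes about 90–93% at 0.80 and 82–91% at 0.90–0.95 when mutations are pooled, or about 90%, 84–85% and 75–78% at 0.80, 0.90 and 0.95 at pair level. It has no width when all mutations are transmitted.

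Independently of the reporting choice, the 82% power in 5.c.3 depends on the approximation. With the same 17 pairs and p = 0.80, it ranges from 82% to over 99.9% according to the interval used, so it says little about the information the pairs will provide.

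These figures assume the plan's Poisson counts and independent mutations. Positive correlation within a source would lower the pooled coverage further. A change is advisable, but the primary analysis is not invalid as written.

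**What to change.** In 5.c.3:

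1. State that the transmission probability will be reported with a Wilson or Clopper-Pearson 95% interval, using an effective sample size that allows for several mutations per source partner. Set the adjustment, or a bounding value, in advance, because the within-source correlation cannot be estimated if every mutation is transmitted. Do not rely on a percentile bootstrap by source, which also collapses to [1, 1] in that case, or on a logit-scale Wald interval, which is then undefined.
2. Replace the 82% power against 1 with the expected interval width or lower limit for 17 pairs, at 0.80 and at values nearer 1. Make the matching change in section 1. Say whether the mutation counts are zero-truncated, since 17 pairs are defined as having at least one mutation in the source, yet 82% was reproduced only without truncation.

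The cost is a few sentences and a re-run simulation, with no change to enrolment, specimens or assays. The interval is somewhat wider near 1, and the sample-size justification becomes a statement of precision instead of power.

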We share the enthusiasm of the reviewers regarding Aim #3. While this is a particularly exciting area of our research, it is important to note that this analysis is inextricably linked to the other project aims. For example, because we cannot study partners at the exact moment of HIV-1 transmission, it is essential for us to determine the duration that low-frequency mutations are detected over time following HIV-1 acquisition (Aim #1). If the source and recipient partners do not have the same pattern of drug resistance mutations, data on the "persistence" of low-frequency mutations (i.e. whether the "prevalence of these presumably transmitted mutations will wane with time") will help us estimate whether the different patterns we observe were actually due to the lack of transmission of mutant virus from the source to recipient partner or due to the overgrowth of the low-frequency mutations by wild-type viruses in the recipient partner in the interval between HIV-1 acquisition and study enrollment.

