Compared to consensus sequencing, OLA identified more subjects with transmitted resistance in both plasma (**4a**, p<.0001, by McNemar's exact test) and PBMCs (**4b**, p=.001). There was not a significant difference in the number of subjects with mutations detected by OLA in plasma and PBMCs (**4d,** p=.3).

***Table 5*** *shows the specific mutations that were detected. No subject had the L74V (NRTI) or D30N (PI) mutations. Four subjects had one HIV-1 drug resistance mutation detected by both consensus sequencing and OLA (one with M184V, two with G190A, and one with L90M). The subject with L90M and two other subjects had intermediate genotypes between wild-type and mutant (T215Q and T215D) that were detected by consensus sequencing; screening for T215F and T215Y by OLA yielded indeterminate results. With the use of OLA, the detection of NRTI resistance increased from 4% to 17% of subjects, the detection of NNRTI resistance increased from 2% to 9% of subjects, the detection of PI resistance increased from 1% to 19% of subjects, and the detection of multi-drug resistant HIV-1 increased from 1% to 9% of subjects. Overall, 34% (95% CI 25-44%) of subjects had transmitted HIV-1 drug resistance. These data show our ability to use OLA to identify transmitted low-frequency HIV-1 drug resistance and demonstrate a high prevalence of drug resistance that was not detected by consensus sequencing in our cohort of subjects with primary HIV-1 infection.*

Table 5: Number of subjects with HIV-1 drug resistance mutations detected by OLA in PBMCs, plasma, or both, by mutation

|  | *NRTI* | | | | *NNRTI* | | | *PI* | | | | |
| --- | --- | --- | --- | --- | --- | --- | --- | --- | --- | --- | --- | --- |
|  | *K65R* | *K70R* | *M184V* | *T215F/Y* | *K103N* | *Y181C* | *G190A* | *I50V* | *V82A/S/T* | *I84V* | *N88D* | *L90M* |
| *PBMCs only* | *4* | *2* | *5* | *5* | *2* | *-* | *1* | *1* | *1* | *-* | *4* | *-* |
| *Plasma only* | *2* | *1* | *2* | *3* | *-* | *4* | *-* | *7* | *-* | *2* | *3* | *-* |
| *Both* | *2* | *-* | *-* | *-* | *-* | *-* | *2* | *-* | *1* | *2* | *-* | *1* |

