**5.c.3 Aim #3: Compare HIV-1 drug resistance patterns in PIC subjects and their source partners.**

This cross-sectional study will evaluate the prevalence and patterns of HIV-1 drug resistance in partner-pairs and compare results of HIV-1 drug resistance testing in the PBMCs, blood plasma, and genital secretions (when available) from the confirmed source partner with test results in PBMCs and blood plasma from the recipient partner. We hypothesize that HIV-1 drug resistant variants will have lower "transmission fitness" compared to wild-type variants, and drug resistance will occur less frequently and at lower levels in the PBMCs and plasma from PIC subjects than in the PBMCs, blood plasma, and genital secretions from their confirmed source partners. Because the most common risk for HIV-1 acquisition reported among our cohort is receptive anal intercourse, the ideal comparison would evaluate the results of HIV-1 drug resistance testing in semen specimens from every source partner. However, not all potential source partners collect genital secretions for study. As previous studies have shown that there is moderate concordance between HIV-1 drug resistance testing results in blood and semen [61-63], our proposed comparison using the results of resistance testing in the blood of source partners should have relevance.

For every subject enrolled in the PIC Cohort study, we will attempt to identify and study all source partners through the methods described below in **5.d.2 PIC Partners study** and **5.e Laboratory methods**.If OLA is not performed as part of the other studies previously described in this application, OLA will be performed on the first available PBMC and plasma specimens from PIC enrollees and on the PBMC, blood plasma, and genital secretions from confirmed source partners. We hypothesize that many but not all mutations in the source partner will be identified in the recipient partner and that low-frequency mutations detected in the recipient partner will be present at lower levels compared to their levels in the source partners. Secondary analyses will explore whether the probability of transmission differs between specific HIV-1 drug resistance mutations.

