**Figure 7: Capture of biotinylated**

**probes on the ELISA plate [1]**

*F*-AC-ATC-CCG-CAG-GGT-TAA-AAA-AAG**-AAC - AAA**-TCA-GTA-ACA-GTA-CTG-GAT-GTG-GGT -*Biotin*

…TG-TAG-GGC-GTC-CCA-ATT-TTT- TTC- TTG - TTT -AGT-CAT- TGT-CAT-GAC-CTA-CAC-CCA…

The ligation products are then captured onto a streptavidin-coated ELISA plate (**Figure 7**), and alkaline phosphatase (AP) labeled anti-fluorescein antibodies and horseradish peroxidase (POD) labeled anti-digoxigenin antibodies are added sequentially. The AP (magenta) and POD (yellow) labeling is quantified by optical density (O.D.) using an ELISA plate reader. In the example above, only mutant virus (magenta) would be detected; however, mixtures of both wild type and mutant viruses are detectable by OLA. Indeterminate reactions occur 2-7% of the time and are typically a result of failure of the ligation reaction due to polymorphisms usually occurring at or adjacent to the two bases to either side of the ligation site. Under those circumstances, no color is produced.

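### Aim 3's only stated detection criterion, a 95% interval that excludes a transmission probability of 1, does not test the hypothesis of lower transmission fitness than wild-type

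*Protocol*

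**What the plan says.** The primary objective of Aim 3 (Section 5.b) is to estimate the probability that source mutations are transmitted. Section 5.c.3 makes the primary analysis a binomial probability, conditional on the number of mutations in the source, and states the hypothesis as lower transmission fitness than wild-type, so that "drug resistance will occur less frequently and at lower levels in the PBMCs and plasma from PIC subjects than in the PBMCs" and the other compartments of the source.

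For sample size, the number of mutations per source is taken as Poisson with mean 2. Each simulated data set "calculates the associated 95% confidence intervals based on normal approximation for the estimated probability", and the criterion is "The type II error is calculated as the number of simulation replicates where the 95% confidence interval contains the value of 1" when the true probability is below 1. Detection therefore means that the interval excludes 1. On that basis "we will have 82% power to detect a transmission probability of all source partner mutations of 80% or less", given "17 confirmed partner-pairs in which the source partner has at least one HIV-1 drug resistance mutation".

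The time between transmission and sampling enters only an exploratory adjustment of the mutation-specific regression. Section 5.c.3 also plans to compare semi-quantitative mutant levels between source and recipient. Section 5.h.4 says the transmission probabilities will feed mathematical models.

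**The concern.** A test of reduced fitness needs a reference for what would be seen with no fitness cost. The criterion takes that reference to be 1. The protocol gives several reasons why observed concordance would be lower even if resistance cost nothing:

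- Section 1 concedes delayed sampling, "because we cannot study partners at the exact moment of HIV-1 transmission", and says wild-type virus may overgrow the mutant in the recipient in the interval.
- Section 3.c describes a transmission bottleneck, while adding that many people acquire mixtures.
- Section 5.e.5 calls a sample mutant only above the 5% control, so a variant just above the threshold in the source can fall just below it in the recipient.
- Section 5.e.5 also says "Indeterminate reactions occur 2-7% of the time", and the pilot tables in Section 4.g count indeterminate results as negative.
- Sources are tested in genital secretions when available, recipients only in PBMCs and blood plasma, and Section 5.c.3 calls blood-semen concordance moderate.

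An interval below 1 could then be taken as reduced transmission fitness when detection, timing or sampling of variants produced it. The same figure would enter the models as a transmission probability.

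**Working it through.** **Set-up.** Let t be the probability that a source mutation is transmitted and s the probability that a transmitted mutation is detected in the recipient. The data inform only the product p = t × s. Simulation: 17 sources; m mutations each, Poisson with mean 2; Binomial(m, p) found in the recipient; success if estimate + 1.96 × SE < 1.

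**The plan's own figure (t = 0.80, s = 1).** The text does not say how the estimate is formed, so four variants were run:

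| Variant | Power |
|---|---|
| Poisson with zeros allowed, mean of per-source proportions | 82% |
| Poisson with zeros allowed, pooled proportion | 91% |
| Zero-truncated Poisson, mean of per-source proportions | 90% |
| Zero-truncated Poisson, pooled proportion | 96% |

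The first reproduces 82%. It draws some sources with no mutations, although the text requires at least one; with truncation the same criterion gives 90-96%, so 82% is conservative for that criterion.

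**No fitness cost (t = 1), imperfect detection.** Chance that the interval excludes 1 (entries vary by up to about one percentage point between runs):

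| s | Zeros allowed, mean (matches 82%) | Zeros allowed, pooled | Truncated, mean | Truncated, pooled |
|---|---|---|---|---|
| 1.00 | 0% | 0% | 0% | 0% |
| 0.964 | 2% | 4% | 3% | 5-6% |
| 0.93 | 14% | 22% | 19% | 30% |
| 0.90 | 31% | 44% | 40% | 56% |
| 0.867 | 51% | 66% | 63% | 77% |
| 0.80 | 82% | 91% | 90% | 96% |

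Because only p = t × s matters, the last row equals the power table: perfect transmission with 80% detection cannot be told apart from the 80% transmission that the study is sized to detect.

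**Where these values of s come from.** In Table 3 (Section 4.f), OLA called 2 of 15 mixtures wild-type, giving 13/15 = 0.867, and 1 of 68 mutant codons was indeterminate. Together the loss is 3/83 = 3.6%, giving 0.964. The value 0.93 corresponds to the upper end of the indeterminate range, 7%. The values 0.90 and 0.80 are assumptions about total loss. The protocol gives no overall figure.

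**How few losses are enough.** Expected mutations: 17 × 2 = 34, or 17 × 2/(1 − e⁻²) = 39 when zeros are excluded. With 34 pooled mutations:

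- 3 not found: 31/34 = 0.912, SE = √(0.912 × 0.088/34) = 0.049, upper limit 1.007, includes 1.
- 4 not found: 30/34 = 0.882, SE = √(0.882 × 0.118/34) = 0.055, upper limit 0.991, excludes 1.

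Four are also enough with 39.

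**Power against a reference below 1** (17 pairs, four variants; the reference values are assumed):

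| Reference | Observed 0.80 | Observed 0.80 × reference |
|---|---|---|
| 0.95 | 44-68% | 63-85% (0.76) |
| 0.90 | 17-30% | 51-74% (0.72) |
| 0.85 | 5-8% | 42-64% (0.68) |

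**The case against.** The criterion sits inside the sample size simulation, while the stated primary objective and primary analysis are estimation. A reader might infer that the study will declare reduced fitness whenever the interval lies below 1. The protocol nowhere says so, and a decision rule could be set in an analysis plan that is not at hand. This stands. The point is that the criterion behind the 82% does not serve the stated hypothesis, not that a false conclusion is built in.

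Part of the remedy is already planned. Section 5.c.3 compares mutant levels between source and recipient, which is also a secondary objective in Section 5.b, and Section 1 expects Aim 1 persistence data to help separate non-transmission from overgrowth. This also stands, but Section 5.c.3 links neither to the primary estimate nor to its power.

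The assay figures must not be stretched:

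- The 0.867 rests on 15 protease mixtures (exact 95% interval for 13/15: 60-98%). Over all 83 codons the loss is 3.6%, where the problem is small.
- Table 5, "Number of subjects with HIV-1 drug resistance mutations detected by OLA in PBMCs, plasma, or both, by mutation", sums to 25 in PBMCs only, 24 in plasma only and 8 in both. A reader might take 8 of 57 as a recipient miss rate and conclude that excluding 1 is nearly certain. That ratio is agreement between compartments. Recipients are tested in both, so it does not measure their sensitivity.
- Section 5.e.5 attributes indeterminate reactions mainly to polymorphisms near the ligation site. Confirmed pairs carry closely related virus, so many could be indeterminate in the source as well and never enter the denominator.
- Equating neutral transmission of a variant with its share in the source assumes a single founder, which Section 3.c qualifies. Majority variants in the source would be little affected by a bottleneck.

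**Conclusion.** The point holds. Excluding 1 is the only detection criterion stated for Aim 3, and it does not test fitness relative to wild-type, because on the protocol's own account 1 is not the value expected without a fitness cost. The size depends on the total loss from assay, compartment, bottleneck and decay, which the protocol does not give. At about 4% loss the interval wrongly excludes 1 in 2-6% of simulations; at 10% it does so in 31-56%, and at 20% in 82-96%. The low end of each range belongs to the variant that reproduces the stated 82%. All figures assume independent mutations with a common detection probability. The estimate itself remains valid as joint transmission and detection, so this calls for a correction to the criterion, the interpretation and the stated power. It is not a reason to abandon the aim.

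**What to change.** 1. State in Section 5.c.3 that excluding 1 is a sizing device and not evidence of reduced transmission fitness.
2. Report the primary estimate with its interval as joint transmission and detection, and carry that label when it is passed to the models in Section 5.h.4.
3. Base any fitness claim on the source-recipient level comparison already planned, with a null of equal mutant share at codons that are mixed in the source, and on a reference concordance below 1 taken from within-person re-detection in pilot and Aim 1 specimens, in line with what Section 1 anticipates.
4. Restate the 82% against that reference, and say how the estimate is formed and whether sources without mutations are drawn.

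The cost is rewording and a new power calculation on data already planned for collection. The price is lower stated power and a more modest claim. One dependency needs planning: the Section 5.g timetable analyses Aim 3 in years 2-3 and Aim 1 in years 3-4, so the Aim 1 part of the reference would arrive later, and pilot specimens would have to supply it first.
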